### Data sources & collection

Recently diagnosed cases will be obtained from the Northern and Yorkshire Cancer Registry and Information Service (NYCRIS) which is the lead registry for colorectal cancer. This cancer registry has linked the NHS BCSP data to the National Cancer Data Repository (NCDR) up until 2010 and is planning to update this linkage on a regular basis. Matching general population controls will be retrieved from the Health & Social Care Information Centre (HSCIC) database at Exeter. Tumour pathology variables will be obtained from the NCDR, including Dukes’ stage of disease at diagnosis which is the only currently nationally available staging variable. Detailed pathology information is also available via the NHS BCSP [8]. Bowel cancer, cervical and breast screening variables will be obtained from the HSCIC.

The data will be checked and cleaned by the PRU Senior Data Manager, transferred to separate Oracle tables, and stored on a UNIX server kept in a secure server room within the Wolfson Institute of Preventive Medicine. Access to the Oracle database is from PCs on the Queen Mary University of London secure network using SQLNET.

All data will be processed in accordance with NHS Information Governance guidelines (NHS IG Toolkit, https://www.igt.hscic.gov.uk/).

### Variables

A list of all the variables to be retrieved for all subjects, cases and controls (where applicable) during the ongoing evaluation study is presented in Table 2. Villousness or high-grade dysplasia, size (≥10 mm) and number of adenomas (≥3) have been found to be the most important predictors of future CRC [24, 25]. Anatomical subsite may also affect risk as sensitivity of investigation methods may differ between location (e.g. see [2] for differences with gFOBt).

**Table 2 Tab2:** **Variables of interest for cases and controls**

Patient characteristics	Primary CRA & CRC pathology variables ^2^	Screening variables ^3^
Patient unique ID	Tumour unique ID	Screening Health Authority cipher (NHAIS)
NHS number	Tumour status	Screening office code
Sex	Tumour description	Screening office reference
Case or control	ICD-10 code	Year of first invitation to bowel cancer screening
	• C18 - Colon	
	• C19 - Rectosigmoid junction	
	• C20 - Rectum	
Date of birth	Dates of diagnoses (all CRAs & CRCs)	**For bowel/cervical/breast screening**
Patient status (Alive or dead at end of study period)^1^	Tumour detection mode (all CRAs & CRCs)	Episode number
Date of death (where applicable)	Anatomical subsite (all CRAs & CRCs)	Episode type
Age at death (where applicable)	CRC Dukes' stage (& any subsequent restaging)	Episode date
Date of *index tumour* diagnosis	CRA villousness	Screen date
Age at *index tumour* diagnosis	Tumour size (all CRAs & CRCs)	End code
Died of primary CRC (where applicable)	Treatment/procedure at diagnosis (all CRAs & CRCs)	Flag: NHS or Screening Programme registration by age 60
Cancer registry	Any further treatment/procedure (all CRAs & CRCs)	
Geographical area (as available in NCDR)	*Optional:* Dates of treatment (all CRAs & CRCs)	
IMD quintile (or postcode)		
Ethnicity		

^1^For cases and controls who died after date of *index diagnosis* of the case.

^2^Those variables will be retrieved for each neoplasia occurrence.

^3^All screening history.

### Power calculation

For the main phase of the study, all cases complying with the selection criteria in the whole of England covering the 2-year evaluation period will be collected. We anticipate biennial accrual of thousands of CRC cases (e.g. 33,218 - 18,590 male and 14,628 female cases - in 2010 [19]), for which statistical power will not be an issue and for which there will be considerable precision.

For the pilot phase of the study, the sample size was estimated to enable sufficient power to answer the primary objective with relative confidence.

Nakajima and collaborators [22] found that the odds ratio of developing advanced stage CRC for those screened within 2 years before the diagnosis versus those not screened using a FIT was 0.76 (95% CI 0.45 – 1.28) when both interval and screen-detected cancers were included in the analysis. We will therefore assume an odds ratio of 0.8 as FIT has been reported to have a higher sensitivity compared to gFOBt (reviewed in [2]).

We anticipate 64% agreement of exposure for matched cases and controls. We further anticipate 55% exposure for cases, 59% for controls. This would imply that for 39% of case–control pairs, both case and control would have been exposed to screening, for 25%, neither would have been exposed, for 16%, the case would have been exposed and not the control, and for 20% the control would have been exposed and not the case (illustrated in Table 3). This would give the expected odds ratio of 0.8. To have 90% power to detect this odds ratio as significant would require 259 discordant pairs and therefore 719 cases with one control per case [26]. As we propose to have two controls per case, 719 cases for the pilot study is considerably more than is strictly needed as the number of potential discordant pairs will be substantially increased.

**Table 3 Tab3:** **Power calculation assumptions around exposure of cases and controls to bowel cancer screening (percentages)**

%	Cases Screened	Cases Not Screened	Total
Controls - Screened	39	20	59
Controls - Not screened	16	25	41
Total	55	45	100

Missing data for tumour pathology variables can be close to 30% with more advanced tumours more likely to have missing pathology data. In a recent retrospective observational study which used NCDR data, Dukes’ staging was available for 75% of the tumours registered between July 2006 and December 2008, however this percentage is likely to increase as time goes on ([name], personal communication).

Ninety percent of symptomatic CRC cases have been shown to be of Duke's stage B or worse [27], but a proportion of 80% at pathological stage B or worse would be a conservative estimate. Thus, only 56% (0.70 [missingness] × 0.80 [stage B+]) of the registered CRC cases will qualify for the study, and we will therefore inflate the sample size to select N cases so that 0.56*N = 719, i.e. around 1,300 cases.

As we require information regarding disease stage and other tumour attributes to select the cases a posteriori, we are planning to collect pilot data from at least 2,000 cases and twice that number of controls as a further failsafe measure. In addition to providing ample power for an odds ratio of 0.8 overall, this will also (1) provide tighter confidence intervals therefore impacting on significance, (2) confer the same power for an odds ratio of 0.7 in a subgroup comprising half the study population (for example in males, females or a particular subsite), and (3) allow for the investigation of the effect of different screening intervals. It is not clear what we should expect in subgroup analyses, but the observed results in the pilot will guide us in terms of the main study.

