To our knowledge, no case–control studies have been published which looked at the effect of gFOBt on CRC incidence. Two studies have been published which assessed the impact of immunochemical faecal blood test (FIT) screening on CRC incidence in Japan, in separate settings [22, 23] but only one of them investigated the effect of FIT on incidence of advanced stage disease [22]. In this study, cases (N = 349) diagnosed with advanced stage CRC (T2-T4 in TNM classification) aged 40 or over were compared to general population controls (3 per case) matched for sex, age and area of residence, with respect to screening history prior to diagnosis. The authors found a significant reduction in the incidence of advanced stage CRC in those who attended screening within 3 years prior to the date of diagnosis (OR = 0.54, 95% CI 0.30 – 0.99). No adjustments were made.

In view of the above, there is a need for a large case–control evaluation of the effect of the NHS BCSP on incidence of advanced stage CRC with appropriate methodology for coping with bias, notably self-selection bias. Meeting the above aims will entail retrieving information on tumour pathology variables, and on screening participation at other national screening programmes. This will be an ongoing biennial evaluation to ensure that the programme continues to deliver the anticipated health benefits, and to potentially improve the programme by identifying good and bad practices.

The case–control design is potentially prone to a number of biases, in particular some that could confer a bias *in favour* of screening; those will be addressed either at the design, or at the analysis stage of the study.

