#### Self-selection (volunteer) bias

Individuals who accept the invitation to screening (attenders) may have an a priori better health status compared with individuals who do not (non-attenders). In the case of bowel screening, gFOBt kit return has been shown to be significantly lower for postcode sectors with poor health [35]. Therefore attenders at screening may be less likely to acquire and potentially die from colorectal cancer. We would anticipate that this will confer a bias *in favour* of screening. Although this bias *in favour* of screening is unavoidable at the design stage, it can be approximately corrected for in the statistical analysis.The regression analyses will be with adjusted for the Index of Multiple Deprivation (IMD), an area-based measure of relative deprivation, derived from residents’ postcodes based on census statistics for overcrowded housing and other factors, and believed to be the main confounding factor relating to both the exposure (i.e. the decision to attend screening), and the outcome.The method developed by Duffy and collaborators [36] will be used *for all patients* to correct the estimated odds ratio using data on participation from the RCTs of CRC screening, in particular data from the Nottingham trial (Individual data obtained for the Nottingham trial from the authors [name] & [name]). In addition, data from regions with population characteristics (total population of screening age 60–69, deprivation, ethnicity, urbanisation status) comparable to areas offered gFOBt screening may be collected from the early stages of the NHS BCSP implementation (e.g. 2006–2007) when the programme had not been fully rolled out [9]. The following estimates may then be derived to potentially help adjust for self-selection bias: (i) CRC incidence among invited (region 1) screened individuals (i.e. risk among attenders), (ii) CRC incidence among invited (region 1) individuals who were not screened (i.e. risk in non-attenders), and (iii) CRC incidence among individuals who were not invited (and not screened, region 2).The method developed by Duffy and collaborators [36] will also be used *for women only* to correct the estimated odds ratio using data on participation in the NHS CSP (cervical) and/or NHS BSP (breast) screening programmes, rather than data on participation from the RCTs of mammographic screening. In the absence of self-selection, the relative risk of primary CRC (death/incidence) associated with bowel cancer screening for non-attenders at cervical or breast screening would be expected to be equal to the relative risk in cervical or breast screening attenders (after adjusting for bowel cancer screening). In the Nottingham RCT, the incidence of primary CRC (all stage) was about 13% higher in non-attenders to bowel cancer screening compared to attenders (Individual data obtained for the Nottingham trial from the authors [name] & [name]). The crucial element in correcting for self-selection bias is the risk ratio for non-attenders versus attenders to breast/cervical screening. Thus the correction is estimated only from data on women as both other screening programmes apply to women only. This will be calculated for women who attended bowel screening at least once and for women who did not attend a single screen, to control for attendance at bowel cancer screening. A range of denominator values for the risk ratio will be assessed for sensitivity. One could compare primary CRC rates (i) in women who have had breast/cervical screening - but not bowel screening -with women who have had neither breast/cervical nor bowel screening; and (ii) in women who have had *both* breast/cervical and bowel screening with women who have only had bowel screening.

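### The pilot's power is worked out only for an uncorrected odds ratio of 0.8, although the protocol plans a self-selection correction that moves the odds ratio towards 1

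*Protocol article*

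**What the plan says.** In the Power calculation section, the planning value starts from a case-control study of FIT screening in which the odds ratio "was 0.76 (95% CI 0.45 – 1.28) when both interval and screen-detected cancers were included in the analysis". The protocol then rounds it, on the ground that FIT is reported to be more sensitive than gFOBt: "We will therefore assume an odds ratio of 0.8". The Background describes the same cited study and says of it: "No adjustments were made".

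The sizing is: "To have 90% power to detect this odds ratio as significant would require 259 discordant pairs and therefore 719 cases with one control per case". After allowing for missing stage and for early-stage tumours (56% of registered cases qualify), the protocol plans at least 2,000 registered pilot cases with two controls each and concludes: "In addition to providing ample power for an odds ratio of 0.8 overall". It describes the pilot as sized to answer the primary objective.

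The section on exposure-opportunity bias ends by calling self-selection the major source of bias in this kind of study. The section on self-selection says the bias is expected to favour screening and that the estimated odds ratio will be corrected for it in all patients. It reports from the Nottingham trial that "the incidence of primary CRC (all stage) was about 13% higher in non-attenders to bowel cancer screening compared to attenders". The Abstract also commits to the correction, and Statistical methods refers back to it. The Power calculation section does not mention it.

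**The concern.** An odds ratio from an unadjusted comparison of screened and unscreened people still contains any self-selection. Power calculated for it is power to show an association on a scale that the protocol itself regards as biased in favour of screening. Correcting a value of 0.8 towards 1 brings it closer to the null while its standard error stays at least as large, so power falls.

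A reader told that power is ample for the primary objective may expect a decisive corrected result from the pilot. If the corrected interval then includes 1, that reader may take it as evidence against the programme, or may fall back on the uncorrected odds ratio.

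**Working it through.** **Inputs from the protocol**
- Uncorrected odds ratio 0.8. Discordant pairs 16% (case exposed only) and 20% (control exposed only), 36% in all (Power calculation, Table 3).
- Two controls per case (Study design & objectives).
- Qualifying pilot cases: 0.56 × 2,000 = 1,120.
- Illustrative self-selection factor 1.13 (Self-selection section).

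**Assumed:** two-sided 5% test (the protocol does not state the level); correction factor known without error; two controls give 4/3 of the information from one.

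**Step 1. The protocol's own figure.** With p = OR/(1 + OR), the discordant pairs needed are

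n = [1.96 × 0.5 + 1.2816 × √(p(1 − p))]² / (p − 0.5)².

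At OR 0.8, p = 0.4444 and √(p(1 − p)) = 0.4969. So n = (0.980 + 0.637)² / 0.05556² ≈ 847 pairs, or 847/0.36 ≈ 2,353 cases with one control each. The stated 259 pairs and 719 cases are not reproduced. A one-sided test still needs 690 pairs. With 259 pairs, two-sided power at 0.8 is about 43%. The figure 259 matches an odds ratio of 2/3 (258.5 pairs).

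**Step 2. Standard error with two controls per case.** Per case, the variance factor for single pairs is 1/0.16 + 1/0.20 = 11.25. Hence

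SE(log OR) = √(0.75 × 11.25 / N).

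At N = 1,120 this is 0.0868.

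**Step 3. Corrected odds ratio.** If the 13% is entirely self-selection, the corrected value is 0.8 × 1.13 = 0.904.

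**Step 4. Power at 1,120 qualifying cases**, as Φ(|ln OR| / 0.0868 − 1.96):

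| Factor | Odds ratio | Power | Expected 95% CI |
|---|---|---|---|
| none | 0.80 | 73% | 0.67 to 0.95 |
| 1.05 (assumed) | 0.84 | 52% | 0.71 to 1.00 |
| 1.13 | 0.904 | 21% | 0.76 to 1.07 |
| 1.20 (assumed) | 0.96 | 7% | 0.81 to 1.14 |

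Simulated conditional logistic regression with two controls per case (3,000 replicates) gave 74% for the uncorrected 0.80 and 22% after the 1.13 correction.

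**Step 5. Does repairing the pair count remove the problem?** At 719 qualifying cases, power at 0.904 is 15%. At about 1,780, where the uncorrected 0.8 does have 90%, it is 31%. So the point stands apart from the miscount. About 8,600 qualifying cases would be needed for 90% at 0.904 (4,129 discordant pairs; 4,129/0.36 × 0.75).

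**Step 6. Main phase.** Two years at the quoted 33,218 cases a year gives 2 × 33,218 × 0.56 ≈ 37,200 cases, and power close to 100% at 0.904. That count is not restricted to the eligible ages or to people invited, but it is more than four times the 8,600 needed.

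**The case against.** Four objections have weight.

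- **The 13% does not fix the corrected value.** It concerns all stages, whereas the primary outcome is Dukes' B or worse. It compares non-attenders with attenders, so it is pure self-selection only if screening left incidence unchanged. The Background supports that only as generally no significant effect. The Abstract names a different ratio for the overall correction, between uninvited controls and non-attending invitees, and does not give its value. If 1.13 were that ratio, the corrected odds ratio at 59% uptake would be 0.8 × 1.13 × 0.59 / (1 − 0.41 × 1.13) ≈ 0.99. This stands: 0.904 is illustrative.
- **A second correction acts the other way.** Exposure-opportunity bias works against screening, and the planning odds ratio included screen-detected cancers. Correcting for it moves the odds ratio away from 1. With a purely assumed factor of 0.90, 0.904 becomes about 0.81 and power about 66%. This also stands, and the documents give no size for it. For 90% power at 1,120 cases the final odds ratio would have to be about 0.755, some 16% below 0.904, and nothing in the protocol supports a shift of that size.
- **The corrected odds ratio is not named as the sole primary estimate.** Correct. But the power is claimed for the primary objective without saying which odds ratio answers it.
- **It is a pilot, and the main phase is national.** Correct. This limits the consequence to what the pilot is said to deliver.

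A reader might go further and infer that the 90% is sound for the uncorrected 0.8 while the study's real answer has power near 20%. The documents support neither half. The 90% fails at 0.8 too, and near 20% follows from one illustrative factor with the opposing correction left out.

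**Conclusion.** The point holds in a limited form. The pilot's power is stated for an uncorrected odds ratio only, while the protocol commits to a self-selection correction that moves it towards 1. With that correction alone, power at 1,120 qualifying cases is about 21% for a factor of 1.13, and between 52% and 7% for factors of 1.05 to 1.20. This rests on a two-sided 5% test, the Table 3 exposure pattern, and a factor treated as known; uncertainty in the factor would lower power further. The fully corrected odds ratio could lie below 0.90, because the size of the exposure-opportunity correction is not given. The documents therefore do not show that the pilot's corrected interval will include 1. They also do not support calling the power ample on the corrected scale. On these inputs the main phase is large enough.

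**What to change.** In the Power calculation section:

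1. Replace the 259 pairs and 719 cases, and the figure of about 1,300 registered cases built on them. For an uncorrected odds ratio of 0.8 at two-sided 5%, about 847 discordant pairs are needed for 90% power, and 1,120 qualifying cases with two controls each give about 73%. This has to come first: labelling the present 90% as the uncorrected power would put a false figure on record.
2. State that this power refers to the uncorrected odds ratio, and drop the claim of ample power.
3. Add power or the expected confidence interval over a range of corrected odds ratios, for example 0.80 to 0.96 and including about 0.90. Note that the self-selection and exposure-opportunity corrections act in opposite directions.
4. Describe the pilot as estimating the corrected effect, and leave the decisive corrected analysis to the national main phase.

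The cost is wording. No extra cases are needed, but the stated pilot power becomes less favourable.

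### The pilot's 90% power claim is wrong: an odds ratio of 0.8 needs about 847 discordant pairs, not 259, and 719 matched pairs give about 43% power

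*Protocol article*

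**What the plan says.** All of this is in the Power calculation section of the protocol article, under Methods/Design.

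- Effect size: "We will therefore assume an odds ratio of 0.8", set slightly weaker than a published odds ratio of 0.76 for immunochemical testing.
- Exposure pattern: "We anticipate 64% agreement of exposure for matched cases and controls", with 55% of cases and 59% of controls screened. Table 3 gives the cells: both screened 39%, case only 16%, control only 20%, neither 25%.
- Requirement: "To have 90% power to detect this odds ratio as significant would require 259 discordant pairs and therefore 719 cases", at one control per case. No significance level or sidedness is given.
- Second control: because two controls per case are planned, "719 cases for the pilot study is considerably more than is strictly needed".
- Yield: 0.70 × 0.80 = 56% of registered cases are expected to qualify, so 719 is inflated to around 1,300. At least 2,000 registered cases will be collected as a further safeguard.
- Resulting claims: "In addition to providing ample power for an odds ratio of 0.8 overall", the pilot is also said to "confer the same power for an odds ratio of 0.7 in a subgroup comprising half the study population".

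**The concern.** The two discordant cells, 16% and 20%, are close together. Separating proportions that similar with 90% power takes many hundreds of discordant pairs, so 259 looks too small on sight.

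The section says the pilot was sized to answer the primary objective, and that its results will guide the main study. If the requirement is understated threefold, readers will believe the pilot can reliably detect the assumed effect when it cannot. A non-significant pilot result could then be taken as evidence against benefit when it reflects limited power. The main phase is not affected, because its case numbers are far larger.

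**Working it through.** **Inputs.** From Table 3 and the text: case-only cell 0.16, control-only cell 0.20, discordance 0.36, odds ratio 0.16/0.20 = 0.8, power 90%. Assumed, because not stated: two-sided 5%.

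**Formula for discordant pairs (matched-pair test).** With P the probability that the case is the exposed member of a discordant pair, P = OR/(1 + OR):

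m = [1.96/2 + 1.2816 × √(P(1 − P))]² / (P − 0.5)²

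**Reproducing the stated figure.** 259 is obtained with P = 0.40, an odds ratio of 0.667:

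m = [0.980 + 1.2816 × 0.4899]² / 0.10² = 1.6078² / 0.01 = 258.5, rounded up to 259.

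The next step in the protocol, 259/0.36 = 719, is internally consistent. That a wrong effect size was entered is an inference from this match; the error stands without it.

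**The stated inputs.** P = 16/36 = 0.4444:

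m = [0.980 + 1.2816 × 0.4969]² / 0.05556² = 1.6168² / 0.003086 = 846.9, so 847 discordant pairs.

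Pairs needed: 846.9/0.36 ≈ 2,353. The requirement is understated by a factor of 847/259 = 3.3. Unconditional matched-pair formulas (Connor, Miettinen) give 2,360 and 2,354 pairs.

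**Does another convention give 259 at an odds ratio of 0.8?** No:

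| Convention | Discordant pairs |
|---|---|
| Two-sided 5%, 90% power | 847 |
| One-sided 5%, 90% power | 690 |
| Two-sided 5%, 80% power | 633 |
| One-sided 10%, 80% power | 361–363 |

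Continuity-corrected, log-odds-ratio and unpooled-variance versions do not come near 259 either.

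**Power of 719 pairs at an odds ratio of 0.8.**

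z = (√259 × 0.05556 − 0.980)/0.4969 = (0.894 − 0.980)/0.4969 = −0.173, so power = 43% (exact binomial 42%).

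**Two controls per case.** Near the null, M controls carry 2M/(M + 1) times the information of one, which is 4/3 for M = 2. Replacing m by N × 0.36 × 4/3 in the power formula gives the third column below. The fourth is from simulated 1:2 conditional analyses under a random-intercept exposure model calibrated to Table 3.

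| Matched sets | OR | Power, 4/3 rule | Power, simulated |
|---|---|---|---|
| 719 | 0.8 | 54% | 54–56% |
| 1,120 (2,000 × 0.56) | 0.8 | 73% | 72–74% |
| 1,350 (2,000 × 0.675) | 0.8 | 81% | 81% |
| 2,000 (all qualify) | 0.8 | 93% | 93% |
| 560 (half of 1,120) | 0.7 | 83% | 82–83% |

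Sets needed for 90% at 0.8: 2,353 × 3/4 ≈ 1,765 by the rule, and about 1,750–1,800 by simulation. At 56% yield that is about 3,200 registered cases (1,765/0.56 = 3,152; 1,800/0.56 = 3,214). With 1,120 sets, the odds ratio detectable with 90% power is about 0.755.

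**The case against.** No one can get 259 from an odds ratio of 0.8, so the defence concerns how far the error reaches.

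- **The 43% is for one control per case.** The plan has two controls and at least 2,000 registered cases, so 43% is not the power of the pilot as collected. This is right. The quoted sentence, however, is itself about one control per case, and the planned pilot still falls short at about 73%.
- **The 56% yield is deliberately cautious.** The section cites 90% stage B or worse among symptomatic cases and 75% staging availability, expected to rise. At 0.75 × 0.90 = 67.5%, 2,000 cases give 1,350 sets and about 81% power for 0.8. In a half-size subgroup (675 sets) at 0.7, power is about 89%. This stands as a qualification: the subgroup claim nearly holds at the higher yield, and the overall shortfall becomes moderate. Power for 0.8 is still below 90%.
- **The 2,000 is a round safeguard with no formula behind it.** Fair. The figures that derive directly from 259 are 719 and 1,300. The adequacy of 2,000 was nevertheless judged against them.
- **The two-control figures need an assumption the protocol does not make**, about how exposure clusters within a matched set. This is true, and simulation runs differ by a point or two. The one-control figures (847; 2,353; 43%) do not depend on it.
- **Misreading of a null pilot is a possibility, not a certainty.** Agreed; the main phase would follow in any case.

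**Conclusion.** The concern holds. The stated 259 discordant pairs and 719 cases do not give 90% power for an odds ratio of 0.8. The section's own Table 3 requires about 847 discordant pairs and about 2,353 cases at one control each. At 0.8, 719 pairs have about 43% power with one control and about 54–56% with two, so the remark that 719 exceeds the need is also wrong.

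For the pilot as planned, power is about 73% at the protocol's 56% yield, and about 81% at a more favourable 67.5%. A true odds ratio of 0.8 would therefore be missed in roughly one pilot in four or five. The subgroup claim is short by about 7–8 percentage points at the 56% yield.

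These results assume two-sided 5%, and the two-control figures also assume a random-intercept exposure pattern matched to Table 3. No conventional significance level rescues 259. Because this is the only sample-size calculation given for the pilot, it must be corrected.

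**What to change.** Rewrite the Power calculation section as follows.

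1. State the significance level and sidedness.
2. Replace 259 and 719 with 847 discordant pairs and about 2,353 cases at one control per case, or about 1,800 qualifying cases with two controls. Remove the derived figure of around 1,300.
3. State what the planned collection delivers: 2,000 registered cases at 56% yield give about 1,120 sets, with about 73% power for an odds ratio of 0.8, 90% power for about 0.755, and about 82% for 0.7 in a half-size subgroup. Mark the two-control figures as approximate and name the clustering assumption. Giving the 67.5% yield alongside (1,350 sets, about 81%) would show the range.
4. Delete the statement that 719 cases is more than needed and the claim of ample power, and reword the subgroup claim to match item 3.

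The cost is a rewrite of one section and a less favourable power statement. No additional subjects are required. If 90% power for 0.8 is still wanted in the pilot, about 3,200 registered cases would have to be collected at the 56% yield; that is a separate choice for the study team.
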